## Participant Timeline - Intervention Phase

### Informed consent

#### Study Participants (People living with HIV who smoke)

Individuals who present at the study clinic will be screened for study eligibility. Those found to be eligible will be linked to a research assistant stationed within the same clinic who will lead them through the informed consent process and then offer enrollment to those interested in participating in the study. The informed consent process will be completed on a first come, first serve basis prior to the

completion of any study specific activities. A research assistant will provide a printed version of the signed informed consent form to each participant as well as any study information the participant requests to have printed. The written consent will be provided in the participant's choice of English or Setswana and administered by trained research assistants. Research assistants will review the document with each participant in a private environment, respond to questions, and emphasize participant rights regarding research participation. Research assistants will use assessment tests in the consent process to ensure that participants understand the study and are able to provide informed consent. (The ability to provide informed consent is one of the inclusion criteria for this study). Participants will have the right to withdraw participation at any time, without interruption to their health and HIV care and treatment services rendered at the health facility.

#### LHW case managers and nurse prescribers

LHW case managers and nurse prescribers participating in the BSMART study will be asked to participate in Focus Group Discussions to obtain feedback on their experiences with integrating the BSMART intervention (Screening, brief intervention, and referral to treatment - SBIRT) into their work with a view to improve the process. A research assistant will lead them through the informed consent process and then offer enrollment to those interested in participating in the study. The research assistant will provide a printed version of the signed informed consent to each participant as well as any study information the participant requests to have printed. The written consent will be provided in the participant's choice of English or Setswana. Research assistants will review the document with each participant in a private environment, respond to questions, and emphasize participant rights regarding research participation. LHWs and Nurse prescribers have the right to decline participation or to withdraw at any time without affecting their employment or any of their rights or benefits.

#### Enrollment in BSMART study

At enrollment, research assistants will fill the demographic questionnaire, intake smoking history questionnaire and use the stages of change algorithm and readiness ruler to determine the individual's stage of change for quitting.

### Provision of SBIRT by LHW case managers

Trained lay health workers will provide the SBIRT intervention (the 5“A”s) to enrolled participants in a private place in the HIV clinic. For participants not ready to make a quit attempt, the LHW will encourage consideration of quitting and arrange for a follow-up conversation.

### Evaluation by nurse practitioners prior to varenicline use

Prior to being prescribed varenicline, eligible participants will be evaluated by a nurse prescriber to assess their suitability. Only eligible patients without any contra-indications to varenicline use will be prescribed varenicline.

### Provision of varenicline

Participants referred for treatment with varenicline will be taught the correct use of varenicline by the nurse prescriber/ dispenser (NPD) at the site where the participant receives care. Participants will initiate medication treatment with varenicline for smoking cessation with a quit date scheduled for day 8 following the first study dose of the medication. Participants will meet with the NPD at baseline who will evaluate them, provide medical clearance and sign off on prescription orders if they meet the requirements for varenicline use (See Appendix IX). Varenicline will be prescribed in accordance with package labeling and provided to participants by the nurse prescriber/ dispenser. Participants will receive a weekly supply of medication for the first four weeks to ensure proper dosing and monitoring for adverse events. For the subsequent eight weeks, participants will return every 4 weeks to receive the next month’s supply of medication. Dosage adjustments will be permitted in an effort to control adverse effects throughout the trial. This will allow us to balance internal validity with good clinical practice.

### Monitoring for adverse events

Adverse event monitoring will be provided by the nurse prescriber/dispenser every time a participant picks up their medication.

## Retention

We will leverage the current approach which utilizes lay health workers and expert clients to ensure retention in the study and include additional strategies such as information leaflets about the importance of retention, appointment cards, motivational text messages, and phone calls (and home visits) to remind participants of appointments. All participants who miss study visits will be contacted.

| Table 3: Participant Timeline - Intervention Phase |                    |          |     |     |     |     |     |     |     |     |      |      |
|----------------------------------------------------|--------------------|----------|-----|-----|-----|-----|-----|-----|-----|-----|------|------|
|                                                    | Responsible person | Baseline | W 1 | W 2 | W 3 | W 4 | W 5 | W 6 | W 7 | W 8 | W 12 | W 24 |
| Screening of participants                          | LHW case manager   | X        |     |     |     |     |     |     |     |     |      |      |
| Informed Consent                                   | Research Assistant | X        |     |     |     |     |     |     |     |     |      |      |
| Enrollment in BSMART study                         | Research Assistant | X        |     |     |     |     |     |     |     |     |      |      |
| Intake Smoking Questionnaire                       | Research Assistant | X        |     |     |     |     |     |     |     |     |      |      |
| Follow-up smoking questionnaire                    | Research Assistant |          |     |     |     | X   |     |     |     |     | X    | X    |
| Stages of change                                   | Research Assistant | X        |     |     |     | X   |     |     |     |     | X    | X    |
| SBIRT Intervention                                 | LHW case manager   | X        |     |     |     |     |     |     |     |     |      |      |
| Breath CO                                          | Research Assistant | X        |     |     |     |     |     |     |     |     | X    | X    |
| Adherence to varenicline                           | Nurse prescribers  |          | X   | X   | X   | X   |     |     |     | X   |      |      |
| Adverse events monitoring                          | Nurse prescribers  |          | X   | X   | X   | X   | X   | X   | X   | X   |      |      |
| Semi-structured Interview                          |                    |          |     |     |     |     |     |     |     |     |      | X    |

## Process and Outcome Measures

### 1. Clinical Outcomes

Primary Outcome: The clinical effectiveness endpoint at six months is the 7-day point prevalence abstinence from combustible tobacco products validated primarily by breath CO < 6 ppm. The failure for this measure is any smoking (even a puff) during a 7-day window.

#### Secondary Outcomes:

- Quit attempts
- Length of successful quitting during each attempt
- Number of cigarettes currently smoked, and
- Number of days of using combustible tobacco products for at least 24 hours within the past month and the last 3 months.

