### **Hypothesis:**

The BSMART intervention (SBIRT and varenicline) will

- i. Increase the proportion of smokers able to quit smoking
- ii. Increase the number of attempts to quit smoking
- iii. Increase the length of abstinence in failed quit attempts
- iv. Decrease the number of cigarettes smoked every day
- v. Decrease the number of days of using combustible products within the past month
- vi. Decrease the number of days of using combustible products within the past three months in people exposed to the intervention as compared to people in the control phase

**Potential Impact:** Addressing the syndemic between tobacco use and HIV infection in a coordinated manner aligns with the NIH HIV/AIDS priorities for effective cancer control among PLWH in a high HIV prevalence setting. This study is significant because it integrates smoking cessation interventions, which are lacking in sub-Saharan Africa (SSA), into a real-world HIV care system that has been underpinned by a robust PEPFAR/CDC program and leverages long-standing partnerships with Ministry of Health and Wellness and the University of Botswana's Anti-tobacco Network for population, health system, and policy level impact.

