|                                                               |                                                                                                                                                                                                                                                                      |                                                                                                                                                                                                            |
|---------------------------------------------------------------|----------------------------------------------------------------------------------------------------------------------------------------------------------------------------------------------------------------------------------------------------------------------|------------------------------------------------------------------------------------------------------------------------------------------------------------------------------------------------------------|
| 4.                                                            | Since you started smoking regularly, have you ever quit for a period of at least 24 hours?
If No, skip to question 7.                                                                                                                                      |  Yes
 No                                                                                                                                                |
| 5.                                                            | In the last year, how many times have you quit for at least 24 hours? (If more than 9 times, put 9)                                                                                                                                                                  | _____ times                                                                                                                                                                                                |

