| 5. | 
Since your last study visit, have you ever quit for a period of at least 24 hours?
 
If No, skip to Q9.
                                                                                                                                                                                                                                                                                    |  Yes
 No                                                                                                                                                                                                                                                                                                   |
| 6. | 
Since your last study visit, how many times have you quit for at least 24 hours? (If more than 9 times, put 9)
                                                                                                                                                                                                                                                                                         | 
_____ times
                                                                                                                                                                                                                                                                                                                                            |
| 7. | 
After your most recent quit attempt, how long did you stay off cigarettes?
                                                                                                                                                                                                                                                                                                                             |  1-2 days
 A week
 2-4 weeks
 Over 4 weeks                                                                                                                                                                                                           |

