## Staging Algorithms

### Smoking Algorithm

#### CLASSIFICATION OF THE STAGES OF CHANGE FOR SMOKING CESSATION

[figure not shown]

Smoking Stage of Change

Client ID# \_\_\_\_\_

Short Form

Date: \_\_\_\_/\_\_\_\_/\_\_\_\_

Assessment Point: \_\_\_\_\_

1. Are you currently a smoker?

- A) Yes, I currently smoke.
- B) No, I quit within the last 6 months.
- C) No, I quit more than 6 months ago.
- D) No, I have never smoked.

Smokers only:

2. In the last year, how many times have you quit smoking for at least 24 hours? \_\_\_\_\_

3. Are you seriously thinking of quitting smoking?

- A) Yes, within the next 30 days
- B) Yes, within the next 6 months
- C) No, not thinking of quitting

Smoking Stage of Change

Short Form

Scoring Sheet

1. Are you currently a smoker?

- A) Yes, I currently smoke.
- B) No, I quit within the last 6 months. (ACTION STAGE)
- C) No, I quit more than 6 months ago. (MAINTENANCE STAGE)
- D) No, I have never smoked. (NONSMOKER)

Smokers only:

2. In the last year, how many times have you quit smoking for at least 24 hours? \_\_\_\_\_

3. Are you seriously thinking of quitting smoking?

- A) Yes, within the next 30 days (PREPARATION STAGE if they have one 24-hour quit attempt in the past year; if there was no quit attempt in the past year, then CONTEMPLATION STAGE)
- B) Yes, within the next 6 months (CONTEMPLATION)
- C) No, not thinking of quitting (PRECONTEMPLATION)

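### The last secondary outcome attaches a 24-hour qualifier to days of tobacco use, so it does not match hypotheses v and vi, and the follow-up form has no item that supplies the count

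*Protocol*

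**What the plan says.** The protocol's Secondary Outcomes list ends with "Number of days of using combustible tobacco products for at least 24 hours within the past month and the last 3 months".

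The Hypothesis section holds the two statements that this outcome is meant to test. Hypothesis v is "Decrease the number of days of using combustible products within the past month". Hypothesis vi is "Decrease the number of days of using combustible products within the past three months". Both name days of use, both predict a decrease, and neither mentions 24 hours.

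The same 24-hour qualifier appears in the smoking instruments, always attached to quitting:

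- Follow-Up Smoking Questionnaire (Appendix B4), item 5: "Since your last study visit, have you ever quit for a period of at least 24 hours"; item 6: "Since your last study visit, how many times have you quit for at least 24 hours".
- Intake Smoking Questionnaire (Appendix B3), item 5: "In the last year, how many times have you quit for at least 24 hours".
- Stages of Change short form (Appendix B5), item 2: "In the last year, how many times have you quit smoking for at least 24 hours".

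For smoking frequency, the follow-up questionnaire has yes/no items on any smoking in the past 30 days and past 7 days, and an item on days of the week smoked with options from 7 down to 1. It has no item counting days over one or three months.

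**The concern.** A qualifier that everywhere else measures how long someone stayed off tobacco has been joined to a count of days on tobacco. The outcome and the hypotheses it serves then name different quantities. Two of the six hypotheses (v and vi) depend on this one line.

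The practical risk is that whoever builds the data set has to decide what the line means. One literal reading carries no information about the intervention. Another turns the scale over, so that a beneficial effect appears as an increase where the hypotheses predict a decrease. The follow-up form gives no help, because no item on it yields the count under any reading.

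**Working it through.** The outcome definition has no stated numerical result to reproduce. The check compares the possible readings of the line with hypotheses v and vi. Let U be the number of days with any combustible tobacco use in a 30-day window.

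**Reading A, word for word: a qualifying day is one with 24 hours of use.** Nobody smokes for 24 hours on end. A daily smoker scores 0 and a complete quitter scores 0, so the contrast between phases is 0.

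**Reading B, the qualifier belongs to abstinence, as in the forms: days without use.** The count is 30 − U. When U falls, the count rises, so the sign is opposite to hypotheses v and vi.

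**Reading C, the qualifier is redundant: a day of use is a day of use.** The count is U. A daily smoker scores 30 over the month (about 91 over three months), a quitter scores 0, and the direction agrees with the hypotheses.

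A variant of C takes the phrase to mean a spell of use lasting a day or more. It agrees with U for daily smokers but not for intermittent ones: a person who smokes on 15 isolated days has U = 15 and may have no qualifying spell.

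**Illustration of size.** Inputs: control abstinence of 10% and an increase of 10 points, both from Power and Sample size. Assumptions that the protocol does not state: every abstainer used nothing for the whole 30 days, and every non-abstainer smoked on d of the 30 days, with d the same in both phases.

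- Mean days of use: control 0.9 × d, implementation 0.8 × d, difference 0.1 × d.
- d = 30: 0.9 × 30 = 27 against 0.8 × 30 = 24, a fall of 3 days.
- d = 15: 0.9 × 15 = 13.5 against 0.8 × 15 = 12, a fall of 1.5 days.

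| Reading | Control (d = 30) | Implementation (d = 30) | Difference | Agrees with hypothesis v? |
|---|---|---|---|---|
| A: 24 hours of use | 0 | 0 | 0 | No contrast |
| B: days abstinent | 30 − 27 = 3 | 30 − 24 = 6 | +3 | Opposite sign |
| C: days of use | 27 | 24 | −3 | Yes |

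B and C are the same 3-day contrast written as 30 − U and U. They hold the same information and differ only in sign and label. Reading A is the one that loses the information.

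**Can the form supply U?** A yes/no item cannot give a number of days. The days-per-week item describes a usual week, has no zero option, and would have to be extrapolated to a month or three months. Neither is a count over the windows that the outcome names.

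**The case against.** The strongest reply is that the intended meaning is not in doubt. The Hypothesis section fixes both the quantity (days of use) and the direction (decrease), and the outcome line shares its noun and both of its windows with those hypotheses. Only one phrase is out of place. The abstinence reading would require replacing the word for use with its opposite, and no sensible analyst would record a 20-a-day smoker as having no days of use. The secondary analyses named under Statistical Analysis for Study Objective 1 (30-day abstinence, stages of change, completion of varenicline) do not use this count, and scoring detail is often settled in a statistical analysis plan, which is not at hand.

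Most of this stands, and it limits the point. A reader might infer that the outcome must be either zero for everyone or reversed in direction, and that the direction of benefit is left open to be chosen once data exist. The documents do not support that. The two literal readings do not exhaust the possibilities, because the phrase can be taken as redundant, and the hypotheses state the direction in advance. The 27 against 24 and 3 against 6 figures are also no measure of harm, since they are one contrast in two forms and rest on assumptions that the protocol does not make.

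Two things survive. The redundant reading works only by ignoring the phrase, which amounts to deleting it. And this is a definition that the protocol states, in words that disagree with its own hypotheses, so it is not a detail merely deferred to another document.

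**Conclusion.** The point holds as an inconsistency in a stated outcome definition. The 24-hour qualifier is attached to use in the outcome list, is absent from hypotheses v and vi, and is used in the smoking forms only for quitting. Applied literally, the outcome does not separate smokers from quitters; read as abstinence, it reverses the expected sign. The hypotheses nevertheless show that days of use, lower being better, is what is meant.

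The reach is limited to one secondary outcome and the two hypotheses that depend on it. The primary outcome, the sample size and the power are unaffected. The conclusion rests on comparing the protocol's texts; the illustrative day counts are not needed for it.

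Correcting the wording alone would not be enough, because the follow-up questionnaire has no item from which the corrected count could be taken.

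**What to change.** 1. In Secondary Outcomes, delete the 24-hour phrase. Define the outcome as the number of days with any use of a combustible tobacco product in the past 30 days and in the past 3 months, scored 0 if there was none, with lower values better. This agrees with hypotheses v and vi.
2. Add matching day-count items to the Follow-Up Smoking Questionnaire (Appendix B4), one for each window. Word them for any combustible product, since the present 30-day and 7-day items ask only about cigarettes.
3. If days abstinent is also wanted, define it as a separate outcome with the opposite expected direction.

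The cost is one line of protocol wording and one or two extra questions per follow-up visit. No change to design, sample size or the primary analysis is needed.

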### 2. Measures to assess the Adoption and Implementation of SBIRT

- Activity Logs: During the implementation period, implementation leaders and care teams will be sent a monthly email requesting that they complete an activity log, which will take 15–30 minutes to complete depending on the number of activities to report. The logs will collect information about implementation activities, intent, duration, and individuals involved. We will ask them to take an inclusive approach and include any activities they believe are related to implementation. We will also add a hypothetical example to the instructions and share a list of discrete implementation strategies. Each month, the research team will invest up to two hours to collect and combine the logs then follow-up with implementation leaders at sites to address their questions.
- Scripts from Focus Group discussions with LHWs
- Responses from SSIs
- SBIRT checklists

### **3. Measures to assess if the BSMART intervention is maintained as part of routine practice over time across HIV care facilities**

RE-AIM measures will be re-assessed at 24 months after BSMART implementation to provide a standardized evaluation approach to understand whether the impact and implementation delivery are maintained and to shed light on where sustainability issues arise e.g. which clinic and populations the implementation is not reaching.

Integrating RE-AIM into quality improvement measures. If BSMART is successful, we will explore building the capacity of each site to use RE-AIM as a tool for institutionalizing quality improvement. Findings will be shared with each site at the end of the maintenance period during learning meetings, and Implementation Leaders will be encouraged to reflect on findings and plan next steps to improve implementation quality. Implementation lessons emerging from other sites will be shared to inform change efforts at other sites. This learning meeting approach will establish feedback loops that allow the intervention to be adapted to ongoing contextual changes.

Multi-level determinants of sustainability. To further identify constructs that are particularly important for sustainability, we will use the 40-item Program Sustainability Assessment Tool to capture measures of coalition, funding stability, partnerships, organizational capacity, program evaluation, program adaptation, communications, and strategic planning in a variety of public health programs during the implementation and maintenance period. Total sustainability score and domain-specific scores will be determined and compared between periods.

